##### Exclusion

The exclusion criteria for families are as follows:
Children who have any known significant developmental disorder or sensory impairment.Families who are referred into the Talking Together programme at the request of external bodies, i.e. safeguarding authorities.Families where the primary carer/parent to whom the intervention programme will be delivered may vary from session to session.

#### Service providers

##### Inclusion

The inclusion criterion for service providers is as follows:
Staff must be LDWs or senior staff involved in the administration and delivery of the Talking Together programme at BHT Early Education and Training.

##### Exclusion

The exclusion criterion for service providers is as follows:
Staff who were not involved with Talking Together in the Better Start Bradford reach area during the time of recruitment to the trial.

### Recruitment and randomisation

#### Sample size

Based on existing recruitment data, over the 9-month period of recruitment, we would expect BHT Education and Training to screen approximately 670 families and refer approximately 250 families to the Talking Together programme, although not all of these families will be eligible for the trial or consent to take part. Recommendations for feasibility studies suggest that at least 30 participants per group will allow sufficient precision when estimating study summary measures [20, 21]. As such, our minimum required sample size is 60 families. However, we have set a desired sample size of 120 families, which is in excess of the recommended 60 participants for a feasibility study [14, 15], to allow for attrition and provide more confidence that a future definitive trial can be successfully conducted (see Fig. 1) [14]. Currently, all families within Better Start Bradford with children of 2 years of age are offered a language screening home visit. For the purposes of recruitment, the LDWs will provide families with an information sheet and consent form to take part in the trial at the end of these language screening visits if the family is going to be referred to Talking Together and meets the oTTer eligibility criteria. Families who consent to take part in the trial will then be randomly allocated to the intervention group or the waiting control group (see Fig. 2).

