### Measures

#### Primary outcomes

Our primary feasibility outcome is recruitment to the trial. We will record the following:
Number of parents receiving the universal screeningNumber of parents eligible to receive Talking TogetherNumber of parents offered Talking TogetherNumber of parents accepting Talking TogetherNumber of parents eligible for the feasibility studyNumber of parents not eligible for the feasibility study and reason whyNumber of parents approached to take part in the feasibility studyNumber of parents consenting to take part in the feasibility study

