### Progression criteria

Progression to definitive trial will be informed by the results of three main progression criteria, based on Avery et al. [27]. A traffic light system will be used with red as an indication not to progress to trial and green indicating progression to trial. Amber indicates potential progress to trial with careful consideration of why these criteria did not reach green.
Recruitment—we anticipate a minimum of 60% of families identified and offered the intervention will be eligible to participate in the trial, and a minimum of 50% of these eligible families will consent to participate in the trial. These numbers will be assessed cumulatively over the course of the recruitment phase. Progression criteria are as follows:
Eligibility—60% and above = green, 50–60% = amber, and below 50% = redConsent—50% and above = green, 40–50% = amber, and below 40% = redProtocol adherence—families will be administered the quantitative assessment measures at specific time points, ensuring that assessments of the waiting control group align with those of the intervention group. Feasibility of running a trial using this design is dependent on the ability to adhere to the following timeline: pre-test within 1 month of Universal Language Screener, post-test 6 to 10 weeks following pre-test, and follow up at 5.5 months to 6.5 months after pre-test. Progression decisions will therefore be based on percentage adherence rates, i.e. 80% = green, 60–80% = amber, and less than 60% = red.Attrition rates—based on previous reported attrition rates for Talking Together, we have calculated a predicted attrition rate over the course of the trial. Progression decisions will be based on the proportion of the recruited sample that attends the 6-month follow-up, i.e. 80% = green, 70% = amber, and below 70% = red.

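### The recruitment lights are ratios only, so the minimum of 60 families in nine months has no role in the progression rule

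*Protocol article*

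**What the plan says.** The Sample size section starts from the recommendation that "at least 30 participants per group will allow sufficient precision when estimating study summary measures" and concludes: "As such, our minimum required sample size is 60 families". It adds a more ambitious target, "we have set a desired sample size of 120 families", partly to absorb attrition. On supply, the service is expected "over the 9-month period of recruitment" to "screen approximately 670 families and refer approximately 250 families to the Talking Together programme".

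Under Primary outcomes: "Our primary feasibility outcome is recruitment to the trial". What is recorded is a list of counts running from screening to consent. The Aim 1 research questions extend the pathway to randomisation, programme completion and follow-up.

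Under Progression criteria, the recruitment criterion has two lights. The first rests on the expectation that "a minimum of 60% of families identified and offered the intervention will be eligible to participate in the trial"; it is green from 60%, amber from 50% to 60% and red below 50%. The second is consent among eligible families; it is green from 50%, amber from 40% to 50% and red below 40%. The article adds: "These numbers will be assessed cumulatively over the course of the recruitment phase". Timeline adherence and attendance at the six-month follow-up are also judged as percentages. No light refers to 60, to 120, to the number referred, or to families per month.

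**The concern.** A ratio does not change when its numerator and denominator shrink together. If the service refers fewer families than expected, but the same share are eligible and the same share consent, both recruitment lights keep their colour while the number randomised falls. The plan names a minimum number of families and a period in which to recruit them, then leaves both out of the rule meant to judge recruitment.

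The minimum is there to give the feasibility estimates adequate precision. If it is missed, those estimates are less precise than the plan itself requires, including the ones behind the other lights and the definitive sample size. A favourable recruitment colour would not reveal this. The rate at which families enter the study is also information a definitive trial needs, and no threshold is attached to it.

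**Working it through.** **Inputs.** From Sample size: 30 per group, minimum 60, about 250 referrals, nine months. From Progression criteria: green floors of 60% (eligibility), 50% (consent) and 80% (follow-up attendance); amber floors of 50% and 40% for the two recruitment lights. One assumption: the families identified and offered the intervention, the denominator of the eligibility light, are the same group as the 250 expected referrals.

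**The plan's own figure.** 30 per group x 2 groups = 60 families. It reproduces.

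**Yield at the green floors.** 0.60 x 0.50 = 0.30 of families offered.

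**Families recruited when both lights sit exactly at green.**

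| Referrals | Eligible (60%) | Consenting (50%) | Against 60 |
|---|---|---|---|
| 250 (expected) | 150 | 75 | above |
| 200 | 120 | 60 | met exactly |
| 180 | 108 | 54 | 6 short |
| 150 | 90 | 45 | 15 short |

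**Break-even.** 60 / 0.30 = 200 referrals. The shortfall from plan is (250 - 200) / 250 = 20%. Per month, that is 200 / 9 = 22.2 referrals against 250 / 9 = 27.8. Counting in whole families moves the break-even only slightly, to 197 referrals.

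**Amber at full volume.** With both lights at their amber floors, 250 x 0.50 x 0.40 = 50 families, 10 below the minimum with no referral shortfall at all. This needs both lights to be low. With one light at its green floor and the other at its amber floor, 250 x 0.60 x 0.40 = 60 and 250 x 0.50 x 0.50 = 62.5. At 250 referrals the minimum is missed only when the joint yield falls below 60 / 250 = 24%.

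**If 60 means families followed up.** At the 80% green retention floor, 60 / 0.80 = 75 families must be randomised. At the green recruitment floors that takes 75 / 0.30 = 250 referrals, exactly the expected volume, so any shortfall would miss the minimum. Under this reading, 60 randomised would leave 60 x 0.80 = 48 followed up.

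**Pace.** Sixty families in nine months is 60 / 9 = 6.7 per month; 75 is 75 / 9 = 8.3 per month. Both can be compared with what is observed, because the counts and the window are in the plan. Neither appears in a light.

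**The case against.** The strongest reply is that green below 60 requires something the plan gives no reason to expect. The 250 referrals come from a running service's own data, and at that volume two green lights give at least 75 families, 25% above the minimum. This stands, and it limits the point: at the green floors the problem arises only with a referral shortfall of about 20% or more. It does not answer the amber case, which needs no shortfall.

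A reader might infer that recruitment pace is never tested. The documents do not support that. Counts along the pathway are the primary outcome, the Aim 1 questions ask for recruitment rates, the Design section lists referral rates among the monitoring data, and the management team meets monthly. Pace is measurable; it only lacks a progression threshold.

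A reader might also infer that green recruitment lights would commit the team to progress despite a missed minimum. That is too strong. The article says the criteria inform progression, there are two criteria besides recruitment, and an advisory group advises on key methodological decisions. The team could weigh a low count, but nothing in the criteria requires it.

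Nor can the observed pace be turned into a duration for the definitive trial. Its sample size is an output of this study, and the article does not confine it to the present reach area. For the same reason ratios are a defensible choice of criterion: eligibility and consent proportions may carry over to a wider catchment better than raw referral numbers. That supports keeping the ratios, not leaving the count out.

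Finally, the 60 was chosen for precision, not as a pace target. This is fair. The proposed line uses it only as the plan's own minimum; 6.7 per month is that minimum re-expressed, not a rate known to suffice for a definitive trial.

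**Conclusion.** The point holds in a limited form. The Sample size and Progression criteria sections do not contradict each other, but the stated minimum and recruitment window have no role in the rule for the primary feasibility outcome. At the expected 250 referrals, two green lights secure at least 75 families. Below about 200 referrals, two lights at their green floors fall short of 60. Two lights at their amber floors give 50 families even at full volume.

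These figures assume that families offered the intervention are the referred families, that 250 (an approximate figure) is the planned volume, and that 60 means families randomised. If 60 means families followed up, the equivalent is 75 randomised, with no slack at the green floors. This is an inexpensive improvement to the decision rule rather than an error in the sample size.

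**What to change.** Keep the two ratio lights and make three small changes.

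1. Add one volume line to the recruitment criterion under Progression criteria: recruitment cannot be green if fewer than 60 families are randomised in the nine-month period, whatever the two ratios show. An amber result already calls for reflection on why green was missed; the count should be part of it.
2. State in Sample size whether 60 means families randomised or families followed up. If followed up, set the volume line at 75 randomised, from 60 / 0.80 at the green retention floor.
3. Report families referred and families randomised per month, for use in planning the definitive trial.

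No new data are needed: the Primary outcomes list covers the pathway up to consent, the Aim 1 questions add the number randomised, and referral rates are already monitored. The downside is that a green recruitment verdict becomes somewhat harder to reach, and more so if the line is 75.

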**Fig. 1 Fig1:**
[figure not shown]
Flow chart of feasibility study of Talking Together programme

**Fig. 2 Fig2:**
[figure not shown]
Procedure for recruitment and consent in the oTTer feasibility study

Randomisation (1:1) will be carried out by a member of the data management (DM) team within BiB. Statistical software package STATA (‘ralloc’ command) will be used to generate a random list stratified by (a) whether the family was within a specific Children’s Centre reach area, (b) language of delivery (English or not), and (c) whether two or more children will be present during delivery of the intervention, using a block size of eight. Referrals from the LDWs with informed consent to take part in the trial will be entered onto SystmOne, a secure healthcare system managed by BTHFT. Once a week, the DM team will carry out randomisation and enter the allocation details onto SystmOne. The deputy language development programmes manager will then access the randomisation details and allocate families to the research assistants and LDWs as appropriate so that a schedule of assessment and intervention can be devised. It is not possible to fully blind the LDWs, RAs, and post-doctoral research assistant (PDRA). The LDWs and RAs will carry out the assessments with the intervention and control group respectively and therefore cannot be blinded to group membership. The PDRA will only have access to anonymised data, but will know the group allocation of all anonymous participants for the purposes of monitoring trial procedures and data analyses.

#### Qualitative evaluation

For interviews, we will invite all LDWs and a purposive sample of oTTer families to participate. For service provider interviews, we are aiming to recruit a minimum of 50% of LDWs along with all members of the senior staff team involved with the Talking Together programme. For family interviews, we are aiming to recruit 20 to 30 oTTer families (10–15 from the intervention arm, and 10–15 in the waiting control arm) who are representative of the range of diversity in the sample. A purposive sampling framework based on key characteristics of families (e.g. main language spoken to child, ethnicity, group allocation, number of children in home) will be used to identify and invite families in the oTTer study to take part in interviews. Invitations will be made via the LDWs during a routine visit. Consent will be taken at the point of invitation, and it will be made clear that families will be contacted by a RA to arrange an interview. During this follow-up contact, families will be given the opportunity to withdraw consent to take part in the interview, and they will again be reminded of the right to withdraw prior to the start of the interview itself. Interviews will take place in the families own home.

All LDWs and senior staff with responsibility for Talking Together will be approached to take part in interviews once recruitment has finished. All LDWs (approx 15) and senior staff (*n* = 3) will receive a letter from the research team inviting them to participate in interviews. Interviews will be scheduled in discussion with the deputy language development programmes manager to ensure maximum participation with minimum disruption to service. The interviews will be carried out by a PDRA who has not previously worked with the BHT team and who can complete the interviews without the support of an interpreter.

### Measures

#### Primary outcomes

Our primary feasibility outcome is recruitment to the trial. We will record the following:
Number of parents receiving the universal screeningNumber of parents eligible to receive Talking TogetherNumber of parents offered Talking TogetherNumber of parents accepting Talking TogetherNumber of parents eligible for the feasibility studyNumber of parents not eligible for the feasibility study and reason whyNumber of parents approached to take part in the feasibility studyNumber of parents consenting to take part in the feasibility study

#### Secondary outcomes

In order to fully explore feasibility, there are a number of secondary outcomes:
Training and QA
Length of time taken to train staff to deliver Talking TogetherNumber of staff trained to deliver Talking TogetherProgramme delivery quality assurance (collected routinely by BHT)Data collection
Number, proportion, and timing of parent withdrawals from the Talking Together intervention and feasibility study and reasons for withdrawalNumber and proportion of parents with quantitative data at each time pointMissing item level data on intervention outcome measures at each time pointSample size estimation
Difference between arms and 95% confidence intervals for the two main child language measures (see the “Screening measures” section and “Intervention outcome measures” section below) at 6-month follow upAdherence and moderators
Based on Hasson [15], our evaluation will use quantitative and qualitative data to look at adherence and potential moderators. To measure adherence, we will collect data on frequency and number of sessions delivered, and completion rate of families. To explore potential moderators, we will obtain feedback on acceptability of trial procedures provided by parents, LDWs, and senior staff at BHT via interviews; feedback on the acceptability of the programme provided by parents via interview; feedback on ease of delivery of the programme provided by service providers via interview; and data on implementation fidelity through evaluation of quality assurance records.

#### Screening measures

The Universal Language Assessment (baseline) is comprised of two measures, which are used in conjunction with observation of the home and parent-child interaction to inform LDWs’ judgement about referral to the intervention:
BHT Language Screener Measure: this assessment was created by BHT in conjunction with speech and language therapists as well as academic partners. It is comprised of ten statements about children’s current language skills scored on a 3-point scale (the child does not do this yet, does this sometimes, does this often). LDWs also record their specific reason for referring into the programme (language and communication, child behaviour, parent behaviour, home learning environment, supporting a family with complex needs).The Oxford Communication Development Inventory-Short (CDI-Short) [22]: a validated measure of early language development comprised of 100 vocabulary items. Parents complete this with the support of the LDW and indicate words the child can (a) say and (b) understand. This measure is used as an indication of conceptual vocabulary, and parents are asked to indicate which words their child can say and understand in any of the languages they speak. It is a parent-report measure that takes approximately 10 min to complete

#### Intervention outcome measures

One of the goals of this feasibility study is to establish the most suitable measures for use as intervention outcomes. After an extensive search we selected two measures that were suitable in terms of ease of use, time taken to administer, and suitability for use with multilingual families. We recognise the limitations inherent in direct translations of language measures but have selected measures that we are confident have attempted to do this as reliably as possible. All outcome measures will be administered at pre-test, post-test, and follow-up.

Two outcomes will be evaluated to determine which is most suitable as a primary outcome for future definitive trial at 6 months follow-up:
The Oxford Communication Development Inventory-Short (CDI-Short) [22]: This assessment is re-administered as an outcome measure.The WellComm language assessment [23]: a validated, direct, and objective assessment of children’s language development. The measure is completed through questions with parents and observation of the child by the LDW. The assessment can be directly translated into Asian languages up to section 5 (https://www.gl-assessment.co.uk/support/support-videos/wellcomm-support-videos/). Where families are receiving the intervention in a language other than English, the LDW will deliver the WellComm assessment in the primary language of the child.

Three additional measures will be evaluated for feasibility as potential secondary outcomes:
Maternal Object Relations Scale (MORS) [24]: this is a validated self-report measure which assesses parent/carer and child relationships and attachment. LDWs help parents complete the measure, and it will be administered in the dominant language of the parent.Home learning environment questionnaire (HLEQ) [25]: an indicator of the types and frequency of activities in the home shown to be predictive of children’s later language skills. LDWs help parents complete the measure, and it will be administered in the dominant language of the parent. This measure has not currently been validated.Strengths and Difficulties Questionnaire (SDQ) [26]: this is a validated measure of children’s emotional and behavioural adjustment. The scale consists of five subscales: emotional symptoms, conduct problems, hyperactivity/inattention, peer relationship problems, and prosocial behaviour. For the purposes of this study, only the hyperactivity and conduct subscales are administered. It should be noted that while validated as a whole measure, the SDQ not been validated to be used in this way. However, a pragmatic decision was made to reduce the measure to these two subscales as the entire SDQ is too long to administer alongside the other quantitative measures. LDWs help parents complete the measure, and it will be administered in the dominant language of the parent.

### Data collection

As our outcome measures are administered routinely by LDWs, and in order to avoid repeat assessments, data will be collected by both LDWs and research staff. Baseline data will be collected during universal language assessment sessions by LDWs as standard practice. Pre-test and post-test data will be collected by LDWs for the experimental group and RAs for the waiting control group. Six-month follow-up assessments in both treatment arms will be carried out by trained RAs accompanied by a LDW familiar with the family to maintain consistency and make clinical judgements about the need for ongoing input. LDWs and RAs will receive the same training in administering the assessments and will carry out reciprocal observations of assessments. The timeline for assessment can be seen in Fig. 3.

**Fig. 3 Fig3:**

Assessment points and timings for outcome data collection and how they correspond to the timing of the intervention

Qualitative interviews with the service provider and families will be collected by a PDRA not responsible for collecting any other trial data. We will carry out interviews with service providers after recruitment to the trial has ended. All LDWs and members of the Talking Together management team will be invited to take part in these interviews. We will invite a purposive sample of oTTer families to participate in interviews at the end of their follow-up period (approximately 6 months after the baseline assessment). Interviews will be carried out in person or by phone at the convenience of the families. All qualitative work will be completed 24 months after recruitment commenced.

